### Measures

#### Primary outcomes

The incidence of moderate-to-severe pain during the operation. This is defined as the proportion of patients reporting a VAS score > 3 at any of the predefined intraoperative timepoints (trocar insertion, cement injection, or end of procedure). Pain will be assessed using a VAS score (0–10), where a higher score indicates more severe pain.

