### Perioperative management

No premedication will be administered to any patient preoperatively. Furthermore, to eliminate its potential confounding effect on the primary pain outcome, no intraoperative sedative or anxiolytic medications (*e.g*., midazolam, dexmedetomidine) will be administered to patients in either group. This standardization ensures that the reported pain scores directly reflect the analgesic efficacy of the assigned intervention (ESPB or local anesthesia) without the influence of altered sensorium. Upon arrival in the operating room, an intravenous line will be established in the upper limb, and electrocardiographic monitoring (non-invasive blood pressure, electrocardiogram, pulse oximetry) will be connected. Patients will undergo the appropriate interventions according to their assigned group. If the patient’s visual analogue scale (VAS) pain score is >3 during the operation, sufentanil 5 μg will be injected intravenously, up to a maximum of 15 μg. Flurbiprofen ester 100 mg will be injected intravenously before the end of the surgery. When patients experience moderate-to-severe pain (VAS > 3) in the ward, tramadol 50 mg will be injected intravenously.

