### Data collection

Following the provision of written informed consent by the patients, baseline data will be collected. To standardize the procedural timeline and assess the impact of the interventions on workflow, the following time points will be recorded for all patients: the time of entering the operating room (T1), the time of completion of the nerve block or local anesthesia infiltration (T2), the time of surgical skin incision (T3), and the time of leaving the operating room (T4). The ‘anesthesia preparation time’ will be defined as the interval from entering the operating room (T1) to the completion of anesthesia intervention (T2). The ‘total operating-room occupancy time’ will be defined as the interval from entering (T1) to leaving (T4) the operating room. The ‘block-to-incision’ interval (T2 to T3) will also be calculated. The anesthesiologist responsible for the patient’s perioperative management, who is blinded to group assignment, will assess and record the patient’s VAS pain score at three specific timepoints: (1) during trocar insertion into the pedicle, (2) during polymethylmethacrylate bone cement injection, and (3) at the end of the procedure before transferring the patient out of the operating room. The intraoperative incidence of moderate-to-severe pain will be recorded. Postoperatively, the highest intraoperative pain score, patient satisfaction with intraoperative analgesia, and surgeon satisfaction will be obtained. The incidence of rescue analgesia within the first 24 h post-surgery, as well as the time to first mobilization, will be collected by an independent researcher. The incidence of adverse events will be recorded from the initiation of the intervention until patient discharge.

All data will be initially recorded on paper-based CRF. These data will then be entered into an Excel database, with verification performed by two independent individuals. Although an independent data monitoring committee was not established for this single-center trial, data accuracy and protocol adherence will be safeguarded through internal quality control processes under the supervision of the principal investigator and the institutional ethics committee.

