#### Secondary outcomes

Anesthesia preparation time: Defined as the time from patient entry into the operating room to the completion of the assigned anesthesia procedure (ESPB or local infiltration).

Total operating-room occupancy time: Defined as the time from patient entry into to exit from the operating room.

Maximum intraoperative pain score: This will be evaluated using the VAS, ranging from 0 to 10, where higher scores indicated greater pain intensity.

Intraoperative patient satisfaction with analgesia: This will be assessed *via* the VAS, ranging from 0 to 10, with higher scores reflecting greater satisfaction with the pain management provided.

Surgeon satisfaction with analgesia: Surgeon satisfaction will be evaluated using the VAS, ranging from 0 to 10, where higher scores represented greater satisfaction with the analgesia.

Incidence of rescue analgesia within the first 24 h postoperatively: This will be analyzed as a binary outcome (yes/no), representing the proportion of patients requiring any supplemental pain medication within the specified timeframe.

Total perioperative opioid consumption: The total consumption of all rescue opioids administered from the start of the procedure until 24 h postoperatively will be recorded. Intraoperative sufentanil and postoperative tramadol doses will be converted to intravenous morphine milligram equivalents (MME).

Time to first mobilization: This will be defined as the time elapsed until the patient is able to get out of bed for the first time following the procedure.

Incidence of adverse events: Adverse events, including local anesthetic toxicity, hemorrhage, nerve injury or infection, and pneumothorax, will be recorded.

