#### Data analysis

Statistical analysis will be performed using SPSS 27.0. The Shapiro-Wilk test will be used to assess normality. Normally distributed quantitative variables will be expressed as mean ± standard deviation, and compared between two groups using an unpaired *t*-test. Non-normally distributed quantitative variables will be expressed as median (interquartile range), and compared between two groups using the Mann-Whitney *U* test. Categorical variables will be expressed as number (percentage), and compared using the chi-square test or Fisher’s exact test. A *p*-value of less than 0.05 will be considered statistically significant.

All analyses will be conducted on an intention-to-treat basis. Any missing data will be handled based on the pattern and amount of missingness. For the primary outcome (incidence of moderate-to-severe pain), a missing value will be considered a treatment failure (*i.e*., included in the numerator for the incidence calculation) to provide a conservative estimate of the intervention’s effect. For secondary continuous outcomes (*e.g*., VAS scores), if data are missing at random and the proportion is small (<5%), complete-case analysis will be employed. If the proportion is larger, multiple imputation methods will be considered.

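### Intraoperative sufentanil rescue for VAS > 3 is not tied to the three scored moments and is not itself a primary event, so a rescued patient can be counted as a non-event

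*Protocol article*

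**What the plan says.** All references are to the protocol article.

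- **Primary outcomes** names the outcome as "The incidence of moderate-to-severe pain during the operation" and then defines it as the proportion of patients with "VAS score > 3 at any of the predefined intraoperative timepoints (trocar insertion, cement injection, or end of procedure".
- **Data collection** schedules readings at those same moments: the managing anesthesiologist "will assess and record the patient’s VAS pain score at three specific timepoints". The same section adds: "Postoperatively, the highest intraoperative pain score, patient satisfaction with intraoperative analgesia, and surgeon satisfaction will be obtained".
- **Perioperative management** states the rescue trigger: if the patient's "pain score is >3 during the operation, sufentanil" is given intravenously. The trigger does not refer to the three moments.
- **Data analysis** has one special rule for the primary outcome: "a missing value will be considered a treatment failure". It says nothing about rescue.
- **Secondary outcomes** uses intraoperative sufentanil only for opioid consumption: "Intraoperative sufentanil and postoperative tramadol doses will be converted to intravenous morphine milligram equivalents (MME". The rescue-incidence outcome is postoperative: "Incidence of rescue analgesia within the first 24 h postoperatively".

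**The concern.** The rescue threshold and the event threshold are the same, VAS above 3, but they cover different spans of time. Rescue covers the operation; the event covers three points within it. Pain that the protocol recognises and treats between those points is therefore outside the primary outcome.

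Rescue can also affect what is measured next. Sufentanil given between trocar insertion and cement injection may lower the cement score, and sufentanil given before the trocar may lower all three. Rescue is thus an intercurrent event acting on the endpoint, and the article does not say how it is to be handled.

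This is the trial's only primary outcome. Events lost in both arms would cost power. Events lost unequally would bias the estimated difference. The results could also look inconsistent: if the maximum intraoperative score covers the whole procedure, it could exceed 3 in a patient whose primary outcome is negative.

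**Working it through.** **1. The plan's own figure.** The Sample size section gives 70% under local anesthesia, 35% under ESPB, two-sided α = 0.05 and power 0.80. With pooled variance and no continuity correction, and mean proportion (0.70 + 0.35)/2 = 0.525:

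n = [1.960·√(2·0.525·0.475) + 0.842·√(0.70·0.30 + 0.35·0.65)]² / 0.35²
= [1.384 + 0.557]² / 0.1225 ≈ 30.8, so 31 per arm and 62 in all.

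Dropout: 62/0.95 = 65.3, so 66 (33 per arm). The stated size reproduces, so the point does not touch the arithmetic.

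**2. When a patient is misclassified.** Three things must all happen:

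- VAS exceeds 3 at a moment other than the three scored ones, and sufentanil is given.
- VAS is 3 or less at all three scored moments.
- No rule turns the rescue into an event. The sections listed above contain none.

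A patient rescued at a scored moment is already an event and is not affected.

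**3. Size, by assumption.** The documents give no share of events that would be missed. Let m be that share, so that the observed rate is the true rate × (1 − m). Exact power at 33 per arm is the sum, over all pairs (a, b) for which the uncorrected Pearson chi-square gives p < 0.05, of Bin(a; 33, p₁)·Bin(b; 33, p₂).

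| Assumed loss | LA | ESPB | Difference | Exact power |
|---|---|---|---|---|
| None | 70% | 35% | 35 points | 0.86 |
| 5% of events, both arms | 66.5% | 33.25% | 33.25 points | 0.82 |
| 10% of events, both arms | 63% | 31.5% | 31.5 points | 0.78 |
| 10 points, both arms | 60% | 25% | 35 points | 0.86 |

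Proportional loss in both arms costs about 4 to 8 points of power. An equal loss in percentage points costs none.

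**4. Unequal loss.** If 10% of events are missed in the LA arm only, the rates are 63% vs 35% and the difference shrinks from 35 to 28 points. If 10% are missed in the ESPB arm only, they are 70% vs 31.5% and the difference grows to 38.5 points. The documents do not indicate which direction, if either, applies.

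**The case against.** The strongest reply is that the only VAS readings the article schedules are the three that count, taken by the same anesthesiologist who manages the patient. If VAS is asked only then, every rescue follows a counted score above 3 and the gap is empty. This stands as a possibility, and it is why the frequency is unknown. But the rescue rule does not say so, and patients are awake and unsedated, so they can report pain at other times.

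The path to misclassification is also narrow. Two of the scored moments are stimuli that the Introduction treats as main sources of pain, so many patients with pain elsewhere would still be caught at one of them. Pain at fixed moments regardless of rescue is a legitimate endpoint, and sufentanil use is reported in the opioid outcome. That is fair, but the endpoint should then not be labelled as pain over the operation as a whole.

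A reader might infer more than the documents support:

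- *That rescued patients are scored as free of pain.* They would be scored as having no VAS above 3.
- *That skin incision is where the arms differ most, so events are hidden mainly under ESPB.* No section says this. The Interventions section requires at least 20 minutes from block to incision.
- *That the false-positive rate is seriously inflated.* With 60% in both arms and 10 or 20 points hidden under ESPB only, exact rejection is 0.15 or 0.41, against 0.06 with nothing hidden. Both the 60% common rate and the one-sided loss are invented for the example. So is a loss under LA only (60% vs 35%, power 0.58).
- *That flurbiprofen hides events.* It is given in both arms before the end of surgery, and the rule counts a score above 3 at any of the three moments. It therefore cannot erase an event already recorded at trocar insertion or cement injection.
- *That the maximum score is a postoperative recall.* The text says only that it is obtained postoperatively, which may mean extracted from recorded scores.

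**Conclusion.** The point stands in a limited form. The label of the primary outcome, its three-moment definition and the rescue trigger do not match, and no rule makes intraoperative rescue an event. Followed as written, the plan can count a patient treated for the pain under study as having had none of moderate or greater severity.

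The size cannot be established from the documents. It is zero if VAS is asked only at the three moments. Under an assumed loss of 5% to 10% of events in both arms, with the planned rates and 33 per arm, exact power falls from 0.86 to 0.82–0.78. Unequal loss would bias the difference in a direction that cannot be predicted. Large one-sided losses lack a documentary basis and do not support calling this a critical flaw. It should be fixed as a cheap improvement to the sole primary endpoint.

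**What to change.** - Define the primary event as VAS above 3 at any of the three moments **or** any intraoperative sufentanil given for pain. If rescue can in fact only follow one of the three readings, this changes no result; say so in one sentence.
- Record the time and triggering VAS of each rescue on the CRF.
- Derive the maximum intraoperative score from all scores recorded at the time, including the trigger scores, and state this in Data collection and Secondary outcomes.
- Reconcile Perioperative management, Data collection and Primary outcomes so that they describe the same span of time. The rescue rule itself need not change.

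Keep the definition to the rescue the article describes. It does not mention supplementary local anesthetic as an intraoperative rescue, so that should not be built into the endpoint.

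Cost: a sentence in the endpoint definition, one added CRF line, and a possibly slightly higher event rate. Sufentanil doses are already collected for the opioid outcome. If the 70% and 35% rates are taken to refer to the combined event, the sample size stays at 31 per arm (66 in all after dropout).

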#### Secondary outcomes

Anesthesia preparation time: Defined as the time from patient entry into the operating room to the completion of the assigned anesthesia procedure (ESPB or local infiltration).

Total operating-room occupancy time: Defined as the time from patient entry into to exit from the operating room.

Maximum intraoperative pain score: This will be evaluated using the VAS, ranging from 0 to 10, where higher scores indicated greater pain intensity.

Intraoperative patient satisfaction with analgesia: This will be assessed *via* the VAS, ranging from 0 to 10, with higher scores reflecting greater satisfaction with the pain management provided.

Surgeon satisfaction with analgesia: Surgeon satisfaction will be evaluated using the VAS, ranging from 0 to 10, where higher scores represented greater satisfaction with the analgesia.

Incidence of rescue analgesia within the first 24 h postoperatively: This will be analyzed as a binary outcome (yes/no), representing the proportion of patients requiring any supplemental pain medication within the specified timeframe.

Total perioperative opioid consumption: The total consumption of all rescue opioids administered from the start of the procedure until 24 h postoperatively will be recorded. Intraoperative sufentanil and postoperative tramadol doses will be converted to intravenous morphine milligram equivalents (MME).

Time to first mobilization: This will be defined as the time elapsed until the patient is able to get out of bed for the first time following the procedure.

Incidence of adverse events: Adverse events, including local anesthetic toxicity, hemorrhage, nerve injury or infection, and pneumothorax, will be recorded.

#### Data analysis

Statistical analysis will be performed using SPSS 27.0. The Shapiro-Wilk test will be used to assess normality. Normally distributed quantitative variables will be expressed as mean ± standard deviation, and compared between two groups using an unpaired *t*-test. Non-normally distributed quantitative variables will be expressed as median (interquartile range), and compared between two groups using the Mann-Whitney *U* test. Categorical variables will be expressed as number (percentage), and compared using the chi-square test or Fisher’s exact test. A *p*-value of less than 0.05 will be considered statistically significant.

All analyses will be conducted on an intention-to-treat basis. Any missing data will be handled based on the pattern and amount of missingness. For the primary outcome (incidence of moderate-to-severe pain), a missing value will be considered a treatment failure (*i.e*., included in the numerator for the incidence calculation) to provide a conservative estimate of the intervention’s effect. For secondary continuous outcomes (*e.g*., VAS scores), if data are missing at random and the proportion is small (<5%), complete-case analysis will be employed. If the proportion is larger, multiple imputation methods will be considered.

#### Sample size

According to our center’s data, the incidence of moderate-to-severe pain during lumbar PVP under local anesthesia is 70%. Assuming that ESPB can reduce the incidence of moderate-to-severe pain by 50% (*i.e*., to 35%) (Sharma et al., 2024), with α = 0.05, 1 − β = 0.8, and performing a two-sided test, the sample size was calculated to be 62 cases (31 cases per group) using PASS 2023 software. Assuming a dropout rate of 5%, the final number of cases to be included is 66 (33 cases per group).

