## Discussion

The present randomized, single-blind, parallel-group trial is designed to provide the evidence on the effectiveness of ultrasound-guided ESPB for analgesia during lumbar PVP. Although ESPB has proved valuable in lumbar spinal fusion (Lu et al., 2025; Sharma et al., 2024; Zhang et al., 2021), its role in PVP remains largely unexplored. By directly comparing ESPB with routine local infiltration anesthesia, this study seeks to clarify whether a bilateral ESPB can meaningfully reduce the incidence of moderate-to-severe intra-operative pain, improve patient and surgeon satisfaction, and facilitate earlier mobilization without increasing adverse events.

Several design features strengthen the anticipated validity and applicability of the results. First, strict adherence to CONSORT standards, pre-registration and detailed data handling procedures reduce the risk of selective reporting. Second, the sample-size calculation is based on a clinically relevant absolute risk reduction (70% to 35%), ensuring adequate statistical power. Third, clinically pragmatic outcome measures—VAS, rescue-analgesic requirements and time to first mobilization—directly reflect peri-operative care priorities and are easily reproducible in other centers. Finally, performing the block at the surgical vertebral level and using a moderate volume (20 mL of 0.25% ropivacaine per side) mirrors everyday practice (Lu et al., 2025; Sharma et al., 2024; Zhang et al., 2021), increasing external validity. Furthermore, we have implemented a coordinated parallel workflow where surgical preparation occurs simultaneously with the performance of the ESPB, coupled with a mandated minimum block-to-incision interval. This design specifically addresses the potential confounding effect of procedural timing, ensuring that the analgesic efficacy of the ESPB is evaluated after it has reached its peak effect.

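### The sample size removes the 5% dropouts, but the analysis counts them as failures; by the protocol's own formula, power at 33 per arm is then 78.8%, not 80%

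*Protocol article*

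**What the plan says.** The Sample size section takes a control rate from the centre's own data ("the incidence of moderate-to-severe pain during lumbar PVP under local anesthesia is 70"%) and a halving of that rate under ESPB, to 35% ("Assuming that ESPB can reduce the incidence of moderate-to-severe pain by 50"%). The error rates are stated as "with α = 0.05, 1 − β = 0.8, and performing a two-sided test". From these, "the sample size was calculated to be 62 cases (31 cases per group) using PASS 2023 software". The allowance for loss follows: "Assuming a dropout rate of 5%, the final number of cases to be included is 66 (33 cases per group").

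The Data analysis section places every analysis on an intention-to-treat basis. For the primary outcome it adds that "a missing value will be considered a treatment failure", which enters the numerator, and it makes no distinction by arm. On the test it says: "Categorical variables will be expressed as number (percentage), and compared using the chi-square test or" Fisher's exact test. It gives no rule for choosing between the two.

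The Discussion lists the sample-size calculation among the design's strengths, as "ensuring adequate statistical power".

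**The concern.** The two sections treat the same dropouts in opposite ways. Dividing 31 by 0.95 is the standard allowance when dropouts are removed: about 31 evaluable patients per arm remain, and their event rates are still 70% and 35%. Under the missing-as-failure rule nobody is removed. All 33 stay in each denominator, and each dropout adds an event in whichever arm it falls. Both rates rise, and the lower one rises more, so the expected difference narrows. The sample-size section makes no allowance for this.

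At stake is whether the stated 80% power holds under the protocol's own missing-data rule. If it does not, a non-significant result could be read as coming from a slightly better powered trial than was actually run.

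**Working it through.** **Inputs.** Rates 0.70 and 0.35, two-sided α = 0.05, power 0.80, 31 then 33 per arm and 5% dropout come from the Sample size section. The missing-as-failure rule and the two candidate tests come from the Data analysis section. One assumption is added: all 5% of dropouts lack the primary outcome, equally in both arms.

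**Step 1. Reproduce the protocol's figures.** Pooled-variance normal approximation without continuity correction:

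n = [1.960·√(2p̄(1−p̄)) + 0.8416·√(p₁(1−p₁) + p₂(1−p₂))]² / (p₁−p₂)²

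With p̄ = 0.525, the two roots are 0.7062 and 0.6614:

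n = (1.3842 + 0.5567)² / 0.35² = 3.767 / 0.1225 = 30.75, so 31 per arm and 62 in total. Power at 31 is 80.3%.

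31 / 0.95 = 32.6, so 33 per arm and 66 in total. Both stated figures reproduce.

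**Step 2. Apply the missing-data rule.** The expected analysed rate is 0.05 + 0.95p:

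- LA: 0.05 + 0.95 × 0.70 = 0.715
- ESPB: 0.05 + 0.95 × 0.35 = 0.3825

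The difference is 33.25 points instead of 35.

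**Step 3. Same formula at 33 per arm.** With p̄ = 0.54875, the roots are 0.7037 and 0.6633:

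z = (0.3325 × √33 − 1.960 × 0.7037) / 0.6633 = (1.9101 − 1.3793) / 0.6633 = 0.800

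Power = Φ(0.800) = 78.8%. For 80%, n = (1.3793 + 0.5582)² / 0.3325² = 33.96, so 34 per arm (68 in total).

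**Step 4. Vary the missing proportion** (same formula, 33 per arm):

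| Missing, each arm | Power |
|---|---|
| 0% | 82.8% |
| 2% | 81.3% |
| 3% | 80.5% |
| 5% | 78.8% |
| 8% | 76.3% |
| 10% | 74.6% |

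**Step 5. Exact power of the two named tests**, by enumerating every possible 2×2 table:

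| Design | Chi-square, uncorrected | Fisher |
|---|---|---|
| 31 per arm, complete, 70% v 35% | 81.9% | 74.1% |
| 33 per arm, complete, 70% v 35% | 85.6% | 79.0% |
| 33 per arm, 5% missing as failures | 82.0% | 74.4% |

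At 33 per arm the actual type I error of uncorrected chi-square is 5.3% at a common rate of 70% and at most 6.4%, reached near 50%. For Fisher's test the maximum is 3.6%.

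**The case against.** The strongest reply is that the two extra patients per arm do offset the dilution. The protocol's benchmark is 31 complete patients per arm. Against that, 33 per arm with 5% counted as failures has essentially the same exact power under both named tests: 82.0% v 81.9% for chi-square and 74.4% v 74.1% for Fisher. At the planned rates the expected cell counts are about 15 or more, so the usual convention would lead to chi-square, which exceeds 80%. This stands, and it limits the point to a small one. It does not remove it, because the formula behind the protocol's 31 falls from 80.3% at 31 complete to 78.8%, below the stated target.

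A second reply is that the outcome is measured during the procedure and the envelope is opened only once the patient is in the room, so few values should go missing. This also stands. With one missing per arm (1/33, about 3%), the formula gives 80.4%. But 5% is the protocol's own planning figure, and it gives no separate figure for missing primary outcomes.

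A reader might infer something stronger: that because of the missing-data rule, 33 per arm cannot give 80% power at a true two-sided 5% level, so that neither named test delivers both stated figures. The documents do not support blaming the missing-data rule for that. Fisher's test is already at 79.0% with 33 complete patients per arm and 74.1% with 31, and the excess type I error of chi-square is also present with complete data. That gap comes mainly from the choice of test. The protocol states α = 0.05 and a p-value threshold in the ordinary nominal sense, and a slight excess over 5% is a general property of the uncorrected chi-square test at this size.

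**Conclusion.** Wrong as written, but minor. The 62 and 66 are computed correctly; the fault is that the dropout allowance does not match the missing-data rule. Under that rule with 5% missing in each arm, the protocol's formula gives 78.8% power at 33 per arm. That is 1.2 points below the target and one patient per arm short (34 v 33).

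The result rests on true rates of 70% and 35%, on every dropout lacking the intraoperative outcome, and on equal loss in the two arms. At 3% missing or less the formula stays above 80%. The spread between the two named tests under the same rule (82.0% v 74.4%) is larger than the dilution effect by formula, so the unqualified claim of adequate power depends mostly on which test is used.

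**What to change.** Keep 66 patients and change the text in three places.

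1. **Sample size:** state that, with 5% missing counted as failures, the expected analysed rates are 71.5% v 38.25%, and that 33 per arm then gives about 79% power by the same formula.
2. **Data analysis:** say which of the two named tests is primary and quote its exact power under this rule: 82.0% for uncorrected chi-square (noting actual type I error of about 5.3% at a common rate of 70% and at most 6.4%), or 74.4% for Fisher's exact test.
3. **Discussion:** align the statement on statistical power with those figures.

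The cost is a few sentences and a slightly less favourable power statement. No extra patients are needed. An unconditional exact test such as Boschloo's is an option but is not required.
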